### Statistical analysis

The primary analysis will use an intention to treat approach and the secondary analysis will use an on treatment approach. The rate of decline of eGFR in ml/min/1.73 m^2^/month will be compared between atorvastatin treated subjects and the placebo group using a two-tailed independent t test. Significance will be deemed p < 0.05.

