### Sample size calculation

The following assumptions were made for the sample size calculation. The rate of decline of eGFR, based on the expected population to be recruited in the LORD trial and a similar trial [3], was assumed to be 0.29 ml/min/1.73 m^2^/month. To demonstrate a clinically significant improvement, based on the REIN study, we expected a difference in rate of eGFR decline of 40%, between atorvastatin treated subjects and controls [2]. Thus we assumed that subjects in the atorvastatin group would have a monthly decline of eGFR of 0.17 ml/min/1.73 m^2^. The standard deviation was assumed to be twice the decline (0.24) [3]. Therefore, it was estimated that the study required 63 subjects per group for alpha to equal 0.05 (two-tailed test) and a power (1-β) of 0.80. To achieve this we aimed to recruit 200 subjects into the LORD trial, which allowed for a dropout rate of 60%.

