## Discussion

The objective of the LORD Trial is to assess whether atorvastatin 10 mg can slow the progression of CKD. Measures of oxidative stress and inflammation will be used to assess whether these are concomitantly affected by this statin treatment. If statins slow the progression of CKD, then most CKD patients may benefit from this treatment. Previous studies have been conducted in this area but have been either smaller, open labeled or short duration. Other studies, such as the SHARP study [26], seek to assess the same question however they include the cholesterol absorption inhibitor ezetimibe in the treatment group, which may confuse the nature of the potential effective agent. The measure of eGFR every three months during the three-year trial is another strength of this protocol. We predict atorvastatin will slow the progression of CKD.

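### The unweighted t test on individual eGFR slopes can lose much of the planned power once dropout produces short slopes; a random-slope mixed model on the same data should be primary

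*Protocol article*

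**What the plan says.** The Statistical analysis section fixes both the test and the analysis set. The monthly rate of eGFR decline "will be compared between atorvastatin treated subjects and the placebo group using a two-tailed independent t test", and "The primary analysis will use an intention to treat approach". No weighting of the rates is mentioned.

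The Sample size calculation section gives the planning values. The control decline "was assumed to be 0.29 ml/min/1.73 m^2^/month", and the atorvastatin group is assumed to have a "monthly decline of eGFR of 0.17 ml/min/1.73 m^2". One slope SD, 0.24, serves for all subjects. The result is 63 per group "for alpha to equal 0.05 (two-tailed test) and a power (1-β) of 0.80". The target is 200 recruited, "which allowed for a dropout rate of 60" per cent.

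Table 1 schedules eGFR at baseline and quarterly to month 36, so a completer has 13 values. The Discussion makes a point of this: "The measure of eGFR every three months during the three-year trial is another strength of this protocol". The Withdrawal from Study section adds that subjects who leave will be asked to consent to continued access to their pathology results, in support of the intention-to-treat analysis.

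**The concern.** A slope's precision depends strongly on how long the subject was followed. An independent t test on one slope per subject ignores this, so a noisy slope from two or three early visits counts as much as one from 13 visits. Intention to treat keeps the early leavers in, and their slopes can dominate the between-subject variance.

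The sample size describes a different situation. It needs 63 per group at SD 0.24 and treats dropouts as contributing nothing. The planned number and the planned test therefore do not describe the same analysis. At stake is power for the primary question: a real difference of the planned size could be missed although the quarterly data would have been enough to show it.

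**Working it through.** **1. The plan's own figure.** The difference is 0.29 − 0.17 = 0.12 and the SD is 0.24. n = 2 × (1.960 + 0.842)² × (0.24/0.12)² = 2 × 7.85 × 4 = 62.8, so 63 per group. The stated figure is reproduced. With 100 per arm and no dropout, power is about 94%.

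**2. Dropout covered.** 63 per group is 126 in total, and 1 − 126/200 = 37%. A true 60% loss would need 126/0.40 = 315. The figure of 200 matches 126 × 1.6 = 202. The main case below is therefore 37%.

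**3. Precision of one slope.** The error variance of a least-squares slope is σ²/Sxx, where σ is the within-subject residual SD of eGFR and Sxx the sum of squared time deviations. With k values three months apart, Sxx = 9k(k² − 1)/12.

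| Follow-up | Values | Sxx |
|---|---|---|
| 36 months | 13 | 1638 |
| 12 months | 5 | 90 |
| 6 months | 3 | 18 |
| 3 months | 2 | 4.5 |

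At σ = 4, for illustration, the sampling SD is 4/√1638 = 0.10 for a 36-month slope and 4/√4.5 = 1.89 for a 3-month slope. The planned total SD is 0.24.

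**4. Assumptions not in the documents.** σ is 2 to 5 ml/min/1.73 m². Dropout has a constant hazard unrelated to slope. Every subject with at least two values has a slope. The value 0.24 is taken as the SD of a full 36-month slope, so the true-slope variance is τ² = 0.24² − σ²/1638.

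**5. One cell by hand (σ = 4, 37% dropout, no later results).**
- The chance of staying through each quarter is 0.63^(1/12) = 0.962.
- About 3.8% of subjects have only a baseline value, leaving about 96 slopes per arm. About 3.6% have exactly two values.
- The average of 1/Sxx over subjects with a slope is 0.0125, against 1/1638 = 0.0006 for completers. The two-value subjects alone supply 0.0084 of it.
- Mean slope variance is 0.0478 + 16 × 0.0125 = 0.248, an SD of 0.50 instead of 0.24.
- z = 0.12/√(2 × 0.248/96) = 1.67, and power is Φ(1.67 − 1.96), about 39%. Simulation gives 41%.

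**6. Simulated power, 100 per arm.** The weighted column is a slope contrast weighted by known inverse variances, standing in for the mixed model.

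| Scenario | t test, σ = 2 → 5 | Weighted, σ = 2 → 5 |
|---|---|---|
| No dropout | about 94% | about 94% |
| 37%, no later results | 74% → 29% | 90% → 86% |
| 37%, half of dropouts retrieved | 85% → 53% | 94% → 91% |
| 60%, no later results | 58% → 19% | 87% → 76% |

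Repeat runs under the same assumptions differ by a few percentage points. At σ = 1, t-test power stays at about 88% (37% dropout) and 81% (60%).

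**The case against.** The strongest reply is that withdrawal need not mean a short slope, because the article plans to seek later pathology results. This stands in part. Full retrieval restores about 94% power. With 80% retrieval at 37% dropout, the t test has about 91% at σ = 2, but about 72% at σ = 5. Retrieval depends on consent and cannot supply eGFR after death, which is a listed outcome.

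Second, the article does not say how a slope is computed or whether a minimum follow-up applies. A condensed article may leave that to a fuller document, so its absence is not criticised here. A 12-month minimum would give the t test about 88% to 79% at 37% dropout. That is still below the weighted analysis of all slopes (91% to 87% in the same comparison), and it would drop randomised subjects on a post-randomisation criterion.

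Third, the size of the loss rests on a residual SD and a dropout pattern that the documents do not give. Later dropout would cost less. The 0.24 is taken from a cited trial and is not said to describe completers. If it already contains noise from short slopes, the calculation counts some of that noise twice. These points stand, and the figures are conditional on them.

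A reader might infer that 80% power cannot be reached once anyone drops out. The documents do not support that, as the cases with σ = 1 or high retrieval show. Nor do they support treating 60% as a dropout level that the design can carry. Completers alone would then be 40 per arm, with about 61% power, so part of that shortfall comes from the dropout arithmetic and not from the test.

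**Conclusion.** The point holds as a conditional loss of power. The named test weights all slopes equally, and the single SD of 0.24 makes no allowance for short ones. At 37% dropout, the t test has about 74% to 29% power with no post-withdrawal results and 85% to 53% with half retrieved, for σ from 2 to 5. The precision-weighted analysis has about 86% to 94%. The loss is small if σ is near 1 or retrieval is nearly complete, and there is none without dropout.

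It would go too far to say that a mixed model removes the problem. At 60% dropout with σ = 5 and no retrieval, the weighted analysis falls to about 76%, and subjects with only a baseline value give no slope information in either method. Nothing here shows the t test to be biased: dropout was simulated as unrelated to slope, so the finding concerns precision. The change should be made, because it gives a better use of data that the trial already collects.

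**What to change.** Make the primary analysis a linear mixed model on all eGFR values at their actual sampling dates, including results retrieved after withdrawal. Use fixed effects for time and treatment by time, and a random intercept and slope per subject. Report the treatment-by-time coefficient (ml/min/1.73 m²/month) with its 95% confidence interval. The target stays the same, a difference in monthly rate of decline.

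Keep the t test on individual slopes as a supportive analysis. It makes different assumptions about dropout, but it is no test of missing at random and may itself have low power.

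The cost is a change of analysis wording, with no new data and essentially no loss of power without dropout. The downside is reliance on missing at random given the observed eGFR.

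Separately, reconcile the stated 60% dropout allowance with 63 per group and 200 recruited.

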### Randomization

The Clinical Trial Pharmacist at the Launceston General Hospital, who is independent of the study team, will perform the randomization. Subjects will also be stratified according to three diagnostic groups; glomerulonephritis, diabetes and other diagnoses. Computer generated random numbers will be placed in blocks of 10 by the Clinical Trial Pharmacist and related to a series of drug code numbers. Each drug code assignment block will refer to one of the stratification groups. Data recorded will include the drug code number, which becomes the subjects LORD trial identification number, the patient hospital record number, the date of allocation as well as the diagnosis. The sheet containing the blocks of drug code numbers are given to the clinical trial coordinator who thus is blinded to the allocation performed by the pharmacist. Once the diagnosis is confirmed by the principal investigator the clinical trial coordinator selects the next available drug code number from the relevant stratification block according to diagnostic grouping. The drug code number is then written on the prescription form and given to the subject who then presents it to the pharmacy. This enables the pharmacist (independent of the trial pharmacist) to dispense from the appropriate randomization group. The subject receives a specific purpose numbered LORD Trial plastic container with tablets enclosed, which are indistinguishable whether they contain atorvastatin 10 mg or identical placebo. The randomization code is kept sealed in an opaque envelope in the Launceston General Hospital Pharmacy Department and an identical copy is kept at an off-site location of one of the associate investigators for the duration of the study.

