**Baseline data and follow-up data every three months for 36 months**
eGFR Cockcroft and Gault
eGFR MDRD
24 hour urine creatinine clearance
24 hour urine protein
Weight and blood pressure
Adverse events and concomitant therapy
Laboratory tests
Hematology
Biochemistry
Oxidative stress measures
Inflammation measures
Lipid profile

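### Randomisation is stratified by diagnosis but the primary t test ignores the strata; if diagnosis predicts eGFR decline, the test is somewhat conservative and gives up a few points of power

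*Protocol article*

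**What the plan says.** - **Randomization** section: "Subjects will also be stratified according to three diagnostic groups; glomerulonephritis, diabetes and other diagnoses". Allocation uses blocks of 10, and each block belongs to one diagnostic group.
- **Statistical analysis** section: the primary comparison of the monthly rate of eGFR decline is made "using a two-tailed independent t test" at the 5% level. Neither this section nor any other names a stratum term, a covariate or an adjusted model.
- **Sample size calculation** section: it plans for "63 subjects per group for alpha to equal 0.05 (two-tailed test", and "a power (1-β) of 0.80", using the same unadjusted two-group comparison.
- **Table 1**: eGFR by both equations and "24 hour urine protein" are measured at baseline and every three months, so baseline values are available but do not enter the named test.

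The article gives no reason for choosing diagnosis as the stratification factor and no figure for how strongly it predicts decline.

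**The concern.** Separate blocks for each diagnosis keep the two arms nearly balanced on diagnosis. Differences in decline between diagnoses therefore largely cancel out of the treatment contrast. An independent t test is built for unrestricted allocation and leaves those differences in its error variance. If they exist, the test overstates its own standard error: the confidence interval is wider than it need be, the true type I error is below the nominal 5%, and part of the precision that stratification could deliver is not used.

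The trial is planned at only 80% power for a large assumed effect (a 40% slower decline), so even a few points of power matter. Diagnosis is already recorded at allocation, so using it needs no new data.

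**Working it through.** **Inputs from the Sample size calculation section**
- Control decline: "was assumed to be 0.29 ml/min/1.73 m^2^/month".
- Atorvastatin decline: "monthly decline of eGFR of 0.17 ml/min/1.73 m^2", so the difference is 0.29 − 0.17 = 0.12.
- Standard deviation: "The standard deviation was assumed to be twice the decline (0.24) [3". I use 0.24 as it stands and take it as the overall between-subject SD, including any differences between diagnoses.
- Two-sided 5%, power 80%. Equal allocation is inferred from the equal group sizes.

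**Reproducing the plan's figure**

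n per group = 2 × (1.960 + 0.842)² × (0.24/0.12)² = 62.8, rounded up to 63. This matches. With 63 per group the standard error is 0.24 × √(2/63) = 0.04276, the standardised difference is 0.12/0.04276 = 2.806, and power is Φ(2.806 − 1.960) = 80.1% (79.5% by the exact t calculation).

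**Effect of ignoring the stratum**

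Let R² be the share of slope variance explained by diagnosis. It is not in the document, so the values below are assumptions. With the strata balanced across arms, the true variance of the treatment difference is (1 − R²) times the variance that the t test estimates. Hence:

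- actual size of the t test = 2 × [1 − Φ(1.960/√(1 − R²))]
- power of the t test = Φ((2.806 − 1.960)/√(1 − R²))
- power with the stratum in the model = Φ(2.806/√(1 − R²) − 1.960)

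| Assumed R² | Size, t test | Power, t test | Power, with stratum | Gain (points) |
|---|---|---|---|---|
| 0 | 0.050 | 80.1% | 80.1% | 0 |
| 0.02 | 0.048 | 80.4% | 80.9% | 0.5 |
| 0.05 | 0.044 | 80.7% | 82.1% | 1.4 |
| 0.10 | 0.039 | 81.4% | 84.1% | 2.7 |
| 0.20 | 0.028 | 82.8% | 88.0% | 5.2 |

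The gain is measured against the t test's own power under stratified allocation, which exceeds 80% when R² is above zero.

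**How large is R² = 0.20?** With three equal strata and evenly spaced means (−d, 0, d), the between-stratum variance is 2d²/3. Setting this to 0.20 × 0.24² = 0.01152 gives d = √0.01728 = 0.131. The extreme diagnoses then differ by 0.26 ml/min/1.73 m²/month, against an assumed control mean of 0.29. The top row is therefore demanding.

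**Simulation** (126 subjects, assumed strata of 30/30/40%, permuted blocks of 10, 8,000 to 10,000 runs)

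| Assumed R² | Size, t test | Size, with stratum | Power, t test | Power, with stratum |
|---|---|---|---|---|
| 0 | 0.052 | 0.053 | 78.4% | 78.4% |
| 0.05 | 0.039 | 0.045 | 80.6% | 82.1% |
| 0.10 | 0.041 | 0.051 | 81.1% | 84.2% |
| 0.20 | 0.031 | 0.053 | 81.6% | 87.4% |

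The Monte Carlo standard error of a size near 0.05 is about √(0.05 × 0.95/8000) = 0.0024, so single entries carry noise. The pattern agrees with the formulas.

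**Dropout.** Losing subjects at random from 200 down to 126 (1 − 126/200 = 37%) partly undoes the balance. At R² = 0.10 the simulated size of the t test was then 0.045 (4,000 runs), closer to 0.05.

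**Baseline values.** A covariate that explains 20% of slope variance but was not used in randomisation left the t test's simulated size at 0.047, which is essentially nominal. Power was 79.8% without it and 87.9% with it.

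**The case against.** The strongest reply is that nothing here is invalid. The t test keeps type I error at or below 5%, the treatment estimate is unbiased, and the sample size was set for this same test. All of that stands.

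The size of the effect also depends on a quantity the document does not give. The Randomization section does not say that the diagnostic groups are expected to decline at different rates, and at R² of 0 to 0.02 the loss is nil or negligible. This stands too, and it makes the point conditional.

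A reader might infer four stronger things that the article does not support:
- That the p-value is certainly conservative. It is so only if diagnosis predicts decline.
- That leaving out baseline eGFR and urine protein adds to the conservatism. These were not used in randomisation, so their omission costs power only, and only if they predict decline.
- That adjustment gains 2, 4 or 8 points over 80%. The proper comparator is the t test's own power under stratification.
- That the benefit of stratification is thrown away. Part of it is kept, as the t test's power above 80% shows.

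Finally, the article is condensed, and adjusted supporting analyses may well sit in an analysis plan that is not shown. Unused baseline covariates are therefore no defect here. The stratum is different, because the article itself names the primary test and that test does not match the stated randomisation.

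**Conclusion.** The mismatch between stratified randomisation and an unstratified primary test is in the text. It is a point of efficiency, not of validity, and the 63 per group is sound for the test as named. If diagnosis explains 5% to 20% of slope variance, the t test's actual error is about 0.044 to 0.028, and including the stratum would gain about 1.4 to 5.2 points of power. Random dropout reduces the conservatism, and at 0% there is no effect.

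These figures rest on an assumed R², on 0.24 being the overall SD, on equal allocation and on near-complete balance within strata. Because the simulated cost at R² = 0 is nil, the change is worth making even though R² is unknown.

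**What to change.** Replace the primary t test with a linear model of each subject's rate of decline on treatment and the three-level diagnostic stratum used in randomisation. Apply it to the slope from each eGFR equation. If a mixed model of the repeated values is preferred, include stratum and stratum-by-time. Report the treatment difference from this model as primary and keep the unadjusted t test as supportive.

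Baseline covariates are optional. If they are used, prespecify them, take baseline eGFR from the same equation as the outcome, and, in a mixed model, say whether the baseline measurement also remains an outcome value.

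The cost is a short change of wording, made before unblinding, and 2 degrees of freedom (126 − 2 = 124 becomes 126 − 4 = 122 with 63 per group). No new data are needed. The sample size should stay as it is, since R² is unknown.

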## Discussion

The objective of the LORD Trial is to assess whether atorvastatin 10 mg can slow the progression of CKD. Measures of oxidative stress and inflammation will be used to assess whether these are concomitantly affected by this statin treatment. If statins slow the progression of CKD, then most CKD patients may benefit from this treatment. Previous studies have been conducted in this area but have been either smaller, open labeled or short duration. Other studies, such as the SHARP study [26], seek to assess the same question however they include the cholesterol absorption inhibitor ezetimibe in the treatment group, which may confuse the nature of the potential effective agent. The measure of eGFR every three months during the three-year trial is another strength of this protocol. We predict atorvastatin will slow the progression of CKD.
